### Definitions

Early group: patients receiving botulinum toxin type A (BOTOX) injection immediately after randomization.

Late group: patients receiving placebo injection immediately after randomization and receive BOTOX injection 2 weeks after randomization if the FOIS score < 3.

Retreat group: patients within the “early group” with a score < 3 of FOIS 2 weeks after BOTOX injection and will receive another BOTOX injection.

Figure 1 is a graphical representation of the study design.

**Fig. 1 Fig1:**
[figure not shown]
Graphical representation of the study design

Explanation for choice of comparators:

The comparator will be normal saline (NaCl 0.9%, 0.5 ml). NaCl is the solvent of BOTOX, and therefore is considered a placebo.

### Allocation and randomization

The late group will initially act as the control group for the early group but will receive BTX treatment later if no improvement of FOIS is achieved. Qualified subjects will be randomized (1:1) in a double-blind fashion to the early group or late group (placebo-control). The randomization sequence was generated by a statistician using the Statistical Package for Social Sciences. A number from 1 to 44 was randomly generated and the random envelopes were generated according to the randomization sequence. The principle investigator (PI) is enrolling patients. A nurse who does not join in the assessment and treatment of the participants will assign participants to their allocation according to the random envelopes. Throughout the double-blind phase of the study, patients and investigators will not be informed of the treatment-group assignment. The BOTOX and placebo will be provided in identical syringes, allowing double-blinded administration. One nurse will be responsible for the dilution of BOTOX and placebo. Unblinding is permissible if there are any adverse events, or participants request the termination of the trial. When unblinding becomes necessary, the principal investigator (PI) will report the reason for the unblinding of patients and the associated adverse event (if exist) to the Data Monitoring Committee, who will jointly decide whether to unblind or not. Once unblinded, the participating investigators, the patient and his/her family will be informed of the patient’s allocation by the nurse who know the patient allocation. All interventions, examination results, adverse events, and reasons for unblinding will be documented.

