### Data collection and management

A clinical research associate will ensure that patient inclusion and data collection are in line with the protocol and will check the following variables: patient initials, date of birth, sex, signed consent form, eligibility criteria, date of randomization, treatment assignment, adverse events, and study endpoints. The data will be collected by the clinical research associate on case report forms. The study documents will be stored and kept in a locked and secure office. All personnel involved in data analysis will be masked. Only the PI and the statisticians will have access to the final data set. If the patient drops out, all data before he/she drops out will be recorded, as well as the reason for the patient’s withdraw and any adverse event.

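### The unblinding rule has a broad trigger, no decision criterion and disclosure to all participating investigators, so FOIS assessors can learn the arm before the week-2 primary assessment

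*Protocol article*

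**What the plan says.** All references are to the protocol article.

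**Allocation and randomization.** During the double-blind phase, "patients and investigators will not be informed of the treatment-group assignment". The syringes are identical, and the nurse who allocates takes no part in assessment or treatment. On breaking the code: "Unblinding is permissible if there are any adverse events, or participants request the termination of the trial". The principal investigator reports the reason, and any associated adverse event, "to the Data Monitoring Committee, who will jointly decide whether to unblind or not". On disclosure: "Once unblinded, the participating investigators, the patient and his/her family will be informed".

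**Data collection and management.** The clinical research associate checks a list of variables that includes "date of randomization, treatment assignment, adverse events, and study endpoints". The same section says: "The data will be collected by the clinical research associate on case report forms". On masking it says: "All personnel involved in data analysis will be masked".

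**Other sections that bear on this.** FOIS is the primary outcome (Primary outcomes) and is compared two weeks after each injection (Statistical analyses). A FOIS score below 3 at two weeks leads to a BTX injection in the late group and to a repeat injection in the early group (Definitions). Participants stay in hospital, and conventional dysphagia rehabilitation is allowed throughout (Treatment or intervention).

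**The concern.** Three features of the unblinding rule combine.

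- **Trigger.** It has no threshold of seriousness or severity. The events named under Treatment or intervention include some that may be mild, such as hoarseness or local bleeding.
- **Decision.** The committee step is a real safeguard, but the article does not say what the decision turns on. The only stated grounds are the broad ones that opened the case.
- **Disclosure.** It goes to the participating investigators as a group. Nothing exempts those who score FOIS or read the videofluoroscopy (VFSS), endoscopy (FEES) or manometry (HRM), and nothing requires FOIS to be recorded before the code is broken.

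FOIS records what the patient is eating by mouth. Both the patient's willingness and the team's readiness to advance the diet can move it, so knowledge of the arm could act through behaviour, through co-treatment and through scoring. Because the same score decides who is injected in the second phase, a distorted week-2 score would carry forward.

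A smaller matter is that the clinical research associate's checklist puts treatment assignment next to the endpoints, and the masking statement in that section covers only analysis staff.

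**Working it through.** **1. The plan's own figure.** The only design number is the total of 44 (Sample size estimates: means 2.6 and 4, SDs 1.1 and 1.8, type I error 0.05, power 0.80, 10% loss).
- Difference: 4 − 2.6 = 1.4.
- Common SD: √((1.1² + 1.8²)/2) = √2.225 = 1.492.
- Two-sided t test with the noncentral t distribution: 18 per arm gives power 0.781 and 19 per arm gives 0.804.
- Allowance for loss: 19/0.9 = 21.1, so 22 per arm and 44 in total.

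The figure reproduces, and this point does not affect it.

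**2. The rule, step by step.**
- *What opens a case?* Any adverse event, or a request to stop.
- *Who decides?* The decision is joint and involves the Data Monitoring Committee. No criterion is stated.
- *Who is told?* Participating investigators, patient and family. No role is excluded.
- *When, relative to FOIS?* No order is stated. An event in the first two weeks could lead to disclosure before the primary assessment.

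Followed as written, the rule therefore allows an assessor or the rehabilitation team to know the arm at the week-2 assessment.

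**3. How many patients could be affected?** The article gives no adverse event rates, so these are assumptions. If 5%, 10%, 20% or 30% of the 44 patients had an event, the number meeting the trigger would be 44 × rate = 2.2, 4.4, 8.8 or 13.2. These are patients whose case could be put to the committee. The number actually unblinded would be no larger and could be much smaller.

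**4. What could it do to the primary comparison?** Again an illustration only. Assume no true effect, a fraction *f* of the BTX arm unblinded before scoring, those patients scored *b* points too high, 20 per arm (44 × 0.9 = 39.6 in total, rounded to 40) and SD 1.1.
- Bias in the mean difference = *f* × *b*.
- Noncentrality = *f* × *b* / (1.1 × √(2/20)) = *f* × *b* / 0.348, on 38 degrees of freedom, two-sided 5% test.

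| *f* | *b* | Bias (FOIS points) | Type I error |
|---|---|---|---|
| 0.10 | 0.5 | 0.05 | 5.2% |
| 0.10 | 1 | 0.10 | 5.9% |
| 0.20 | 0.5 | 0.10 | 5.9% |
| 0.20 | 1 | 0.20 | 8.7% |
| 0.30 | 0.5 | 0.15 | 7.1% |
| 0.30 | 1 | 0.30 | 13.4% |

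Against the planned difference of 1.4, the bias runs from 0.05/1.4 = 4% to 0.30/1.4 = 21%. Both *f* and *b*, and the choice to place the error in the BTX arm, are assumed.

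**The case against.** The strongest reply is that the trial already has a gate. An adverse event makes unblinding permissible, not automatic: a reason must be reported, and a committee that the Monitoring section calls independent of sponsors takes part in the decision. That stands, and a reader who infers that every minor event breaks the blind goes beyond the text. What remains is that the decision has no stated criterion and the disclosure list is wider than care requires.

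Three further objections also stand and limit the point.

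- **No contradiction between sections.** A reader might infer that the data-collection section conflicts with the blinding statement, or that the data collector knows the arm of all 44 patients. The article does not say that only the allocating nurse knows the arm. It describes the associate as checking and collecting data, not as scoring FOIS, and checking assignment may mean checking a randomisation number. The wording needs clarifying and no more.
- **No established direction.** A reader might infer that BTX patients would be unblinded more often. No rates by arm are given. Local bleeding can follow the needle in either arm, and aspiration pneumonia is a risk of the dysphagia itself.
- **Requests to stop matter less.** A patient who leaves usually has no later FOIS to bias, so this trigger adds little to the risk.

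It can also be said that a condensed article leaves code-break detail to the full protocol. That would answer a complaint about silence. Here the article states a rule on who may be unblinded and who is then told, and that stated rule is too wide.

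**Conclusion.** The point holds as a cheap improvement. The unblinding rule is broad in its trigger, has no stated criterion for the committee's decision, and discloses to all participating investigators without protecting outcome assessors or the order of FOIS scoring. Disclosure before week 2 can therefore bias a behaviour-dependent primary outcome and the second-phase injection decision that rests on it.

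The size and direction of any bias cannot be derived from the article. The illustrated 0.05 to 0.30 points, with type I error of about 5.2% to 13.4%, rests wholly on assumed unblinding fractions and scoring shifts. The sample size of 44 is not in question. The remark on the clinical research associate is a request for clearer wording.

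**What to change.** **Allocation and randomization.**
- Keep the committee decision, and state that it depends on whether knowledge of the allocation is needed for that patient's care.
- Disclose only to those who need it for that care, and not to the FOIS, VFSS, FEES and HRM assessors.
- Record FOIS before a code break where the patient's condition allows.

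**Data collection and management.** State that during the blinded phase the clinical research associate checks the randomisation number and not BTX or placebo. Alternatively, keep treatment assignment separate from the endpoint forms.

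**Cost.** Wording in the protocol and possibly the case report form. The sample size, visits and analysis do not change. The downside is that some patients and investigators learn the allocation later than under the present rule.

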### Treatment or intervention

The treatment will comprise of administering a BOTOX injection into the cricopharyngeal muscle guided by a combination of catheter balloon, ultrasound, and EMG. The BOTOX will be diluted to 100 U/ml with normal saline. Patients will receive 50 U (diluted in 0.5 ml normal saline) of BOTOX or a placebo (0.5 ml normal saline) in the cricopharyngeal muscle. First, the catheter balloon will be inserted into the esophagus through the nasal cavity, and 4 to 6 ml of water will be injected into the balloon. The balloon will be fixed at the cricopharyngeal muscle when pulled up softly and cannot be pulled up more. One person (speech language pathologist) will hold the catheter and maintain the balloon at this position. Second, ultrasound probe will be placed on the left or right side of the anterior cervical region. Under the guidance of ultrasound, the sternocleidomastoid muscle, thyroid gland, cricopharyngeal muscle, and balloon will be visible. The balloon, as a reference, will be fixed at the distal part of the cricopharyngeal muscle. The concentric EMG needle will be inserted in the marked side under the guidance of ultrasound. When the needle passes through the tissue and reaches the cricopharyngeal muscle, the EMG signal of this muscle can be heard, and then the patient will be instructed to swallow, allowing changes in the EMG signal to be observed and heard. After confirming the position, BOTOX will be injected into the target muscle. Generally, a single injection of botulinum toxin is 50 U. The BTX intervention will be applied by the PI ([name]) assisted by other investigators. Participants will remain hospitalized for the duration of the research. Every concomitant care and conventional dysphagia rehabilitation treatment will be allowed. Novel rehabilitation treatment such as repetitive transcranial magnetic stimulation is prohibited during the trail.

Every effort will be made to improve patient adherence to protocols. In the case of an adverse event following treatment administration (hoarseness, gastroesophageal reflux, local bleeding, aspiration pneumonia), treatment will be immediately discontinued.

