
### Adverse events

Adverse events and unintended effects during the treatment will be reported directly to the sponsor. The investigator will also assess the severity, causality, and seriousness of the adverse events and will inform the Data Monitoring Committee within 3 days of the initial observation of the event. The onset date, manifestations, severity, duration, action taken, and outcome for each adverse event will be recorded. Patients who suffer harm from trial will be cared for and financial compensation will be provided by our department.

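### Every unblinding, even an urgent one for an adverse event, needs a prior Data Monitoring Committee decision, with no urgent exception and no time limit

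*Protocol article*

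**What the plan says.** The Allocation and randomization section sets the blinding rule: during the double-blind phase "patients and investigators will not be informed of the treatment-group assignment". It then defines when the blind may be broken: "Unblinding is permissible if there are any adverse events, or participants request the termination of the trial". For a case where unblinding has become needed, the principal investigator reports the reason and any associated event "to the Data Monitoring Committee, who will jointly decide whether to unblind or not". Disclosure comes last: "Once unblinded, the participating investigators, the patient and his/her family will be informed of the patient’s allocation by the nurse who know the patient allocation".

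The Adverse events section gives the only time limit for contact with the committee about an event. The investigator assesses it and "will inform the Data Monitoring Committee within 3 days of the initial observation of the event".

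Two other sections bear on the point. Treatment or intervention names the events expected after injection and the response: "hoarseness, gastroesophageal reflux, local bleeding, aspiration pneumonia), treatment will be immediately discontinued". The same section says that participants stay in hospital throughout. Drop out criteria gives a severe adverse event as an example of a condition that leads to drop-out.

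**The concern.** A code-break rule has two jobs: to protect the blind against casual disclosure, and to release the allocation when a patient's care cannot wait. The rule here does the first through committee oversight but makes no provision for the second. It places the committee's decision ahead of every disclosure, including one already recognised as needed, and it leaves the committee free to decline.

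The first stake is participant safety. The second is control of the blind. A site with an urgent case would have to wait for a committee decision or go round the rule informally, and the second course leaves no controlled record of who learned what. The third is the scope of disclosure. Once the blind is broken, all participating investigators as well as the patient and family are told, which may include people who will score the Functional Oral Intake Scale two weeks after injection.

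**Working it through.** The point is procedural and no arithmetic applies, so the check sets the sections side by side.

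1. **Trigger.** Any adverse event, or a participant's request to terminate, makes unblinding permissible (Allocation and randomization). Adverse events are therefore plainly within the rule.

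2. **Steps once unblinding is needed.** The order in the same section is: report by the principal investigator, decision involving the committee, disclosure by the nurse. The word jointly could mean the investigator together with the committee, or the committee's members together. On either reading the committee's decision comes before disclosure, and it can be negative.

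3. **Exceptions.** None is stated in that section, in Adverse events or in Monitoring.

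4. **Time limits.** The unblinding rule sets none, either for the report or for the decision. The three-day limit in Adverse events governs general notification of an event. It does not say that an unblinding request must be made sooner, and it does not say that such a request may wait. It therefore neither delays an unblinding request nor guarantees a prompt one.

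5. **Alternative routes to the allocation.** Investigators are blinded. The principal investigator gives the injection, assisted by other investigators (Treatment or intervention). The allocation is known to a nurse who takes no part in assessment or treatment. The text gives the treating team no other way to learn it.

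6. **Whether stopping treatment removes the need.** The listed events lead to immediate discontinuation, and that step can be taken blind. It does not withdraw an injection already given, however, and the unblinding rule itself foresees that an adverse event can make the allocation needed.

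7. **Consequence.** Steps 2 to 5 together mean that, under the rule as written, an urgent disclosure depends on a prior committee decision with no set timing. Allocation could therefore be unavailable when urgent care calls for it. That is a possibility created by the rule, not a measured delay.

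**The case against.** The strongest case against the point has four parts.

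- **The two sections do not conflict.** An investigator who wants to unblind can contact the committee at once, and that report is itself the notification; the three days then apply to other events. This is right. The point is not a contradiction, and it rests on the prior-decision rule alone.

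- **No delay figure is supported.** A reader might join the sections and infer a wait of up to three days plus decision time, or express it as a share of the two weeks between injections (3/14 = 21%). The documents do not support this. Three days is an outer limit for routine notification, no waiting period is attached to an unblinding request, and nothing says an investigator seeking the code would use the whole allowance.

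- **Clinical need is assumed.** No section says that the management of any listed event differs between toxin and saline, and patients are in hospital with concomitant care allowed. This also stands as a limit: harm is not shown, only that the rule blocks prompt access in a case where the protocol itself accepts that unblinding is needed.

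- **Emergency logistics belong in the full protocol.** Call lists and out-of-hours arrangements do, and their absence from an article is no fault. But the article states a positive rule that covers every unblinding. A fuller document would have to override that rule, not merely add detail to it.

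**Conclusion.** The point holds as a defect in a stated rule: disclosure for an adverse event depends on a prior decision involving the committee, which may refuse, with no urgent exception and no timing. It should be corrected because it concerns participant safety and the correction is cheap.

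Its size cannot be given as a number. The documents state no delay, no committee response time and no expected rate of events needing a code break. In principle the rule applies to any of the 44 planned participants during the blinded phase.

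The conclusion assumes that the rule is followed as printed and that no document outside the article overrides it. It does not rest on the three-day limit, and it makes no claim about how any event should be treated.

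**What to change.** Reconcile Allocation and randomization with Adverse events so that the two kinds of request are separated:

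- **Urgent access.** On criteria that the investigators set, the nurse who knows the allocation discloses it to the treating physician without waiting for the committee. The committee is informed afterwards, within the limit already in Adverse events. The reason is documented, as the protocol already requires.
- **All other requests.** The prior joint decision stays as it is.
- **Scope of disclosure.** For an urgent code break, replace the present wide disclosure with one limited enough that those who assess the outcomes remain blinded.
- **Follow-up.** Reconcile with Drop out criteria, which lists a severe adverse event, and state whether a patient unblinded in this way stays in follow-up. Without this, the same patient could be read as both retained and dropped.

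The cost is a few sentences, an amendment to the Ethics Committee and sponsor as the Monitoring section requires, and access to the nurse or the allocation record when an urgent case arises. Neither the sample size nor the analysis changes. Ten participants had been included when the article was submitted, so at that point the change could have covered the remaining 44 − 10 = 34. The small downside is a possible extra code break without prior committee review.

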### Treatment or intervention

The treatment will comprise of administering a BOTOX injection into the cricopharyngeal muscle guided by a combination of catheter balloon, ultrasound, and EMG. The BOTOX will be diluted to 100 U/ml with normal saline. Patients will receive 50 U (diluted in 0.5 ml normal saline) of BOTOX or a placebo (0.5 ml normal saline) in the cricopharyngeal muscle. First, the catheter balloon will be inserted into the esophagus through the nasal cavity, and 4 to 6 ml of water will be injected into the balloon. The balloon will be fixed at the cricopharyngeal muscle when pulled up softly and cannot be pulled up more. One person (speech language pathologist) will hold the catheter and maintain the balloon at this position. Second, ultrasound probe will be placed on the left or right side of the anterior cervical region. Under the guidance of ultrasound, the sternocleidomastoid muscle, thyroid gland, cricopharyngeal muscle, and balloon will be visible. The balloon, as a reference, will be fixed at the distal part of the cricopharyngeal muscle. The concentric EMG needle will be inserted in the marked side under the guidance of ultrasound. When the needle passes through the tissue and reaches the cricopharyngeal muscle, the EMG signal of this muscle can be heard, and then the patient will be instructed to swallow, allowing changes in the EMG signal to be observed and heard. After confirming the position, BOTOX will be injected into the target muscle. Generally, a single injection of botulinum toxin is 50 U. The BTX intervention will be applied by the PI ([name]) assisted by other investigators. Participants will remain hospitalized for the duration of the research. Every concomitant care and conventional dysphagia rehabilitation treatment will be allowed. Novel rehabilitation treatment such as repetitive transcranial magnetic stimulation is prohibited during the trail.

Every effort will be made to improve patient adherence to protocols. In the case of an adverse event following treatment administration (hoarseness, gastroesophageal reflux, local bleeding, aspiration pneumonia), treatment will be immediately discontinued.

